#### Process measures

2.7.3

Intervention adherence rate: the proportion of eligible cases in which both antibiotic initiation assessment and the mandatory 48–72-h reassessment were completed as specified by the intervention protocol.

### Data collection and management

2.8

To ensure data quality and comparability, standardized collection and reporting procedures will be coordinated by the regional steering committee.

#### Data elements and sources

2.8.1

All participating centers collect data across three domains:

Baseline data: Data will be extracted from hospital electronic medical record systems and discharge summaries. Demographic and baseline clinical characteristics of enrolled neonates from both the pre-intervention (historical control) period and the intervention period will be collected, including sex, gestational age, birth weight, admission diagnoses, and comorbidities. In addition to patient-level data, center-level baseline characteristics will be collected for each participating NICU. These characteristics will include local microbiological resistance patterns (antibiograms) and baseline rates of hospital-acquired infections. These data will be used to describe inter-center differences that may influence empirical antibiotic prescribing practices.Process data: collected to calculate process measures, primarily using a standardized Antibiotic Use Case Registry Form. Key variables include a unique study identifier, date and indication for antibiotic initiation, completion of initiation assessment, documentation of the 48–72-h reassessment, and dates and results of blood cultures and other microbiological tests.Outcome data: collected to derive primary and balancing outcomes and extracted from electronic medical records and discharge summaries. These include daily antibiotic administration records (used to calculate antibiotic days), total length of NICU stay, dates and diagnostic basis of LOS, dates and causes of death, and records of antibiotic re-initiation following discontinuation.

#### Data collection and reporting workflow

2.8.2

A “center-based collection with monthly centralized reporting” model is employed:

Local collection: A designated data manager at each hospital extracts and enters data into a uniform Excel template provided by the steering committee.Monthly reporting and audit: Within the first three working days of each month, data managers complete data entry for all eligible cases from the preceding month and submit encrypted Excel files to the regional steering committee. The committee's data management team conducts completeness and logical consistency checks within 1 week (e.g., alignment between antibiotic days and length of stay, internal consistency of calculated indicators). Identified discrepancies are resolved through direct communication with the respective center. After verification, data are aggregated and locked for monthly analysis.

#### Data quality assurance and security

2.8.3

To ensure data quality, the following measures are implemented:

Standardized templates and training: prior to study initiation, all data managers receive standardized training on data definitions, entry procedures, and quality requirements.Source verification and periodic audits: in addition to electronic audits, clinical experts appointed by the regional steering committee conduct quarterly on-site or remote audits at participating centers. Random samples of original medical records are reviewed to verify consistency between registry data and source documentation, and audit findings are incorporated into quality feedback.Data security and confidentiality: all data files are encrypted during transmission and storage. Neonatal information is de-identified using unique study identifiers. The aggregated analytical database is securely maintained by the regional steering committee. Upon study completion, all data will be archived in accordance with applicable regulations.

### Statistical analysis

2.9

To rigorously evaluate whether the QI intervention achieves its intended goals, complementary analytical approaches will be used to establish a coherent chain of evidence. Statistical process control charts (*P*-charts) will first be used to monitor temporal variation in antibiotic use and to distinguish common-cause variation from special-cause variation potentially associated with the intervention. Special-cause variation observed after implementation will be interpreted as process-level evidence supporting intervention-associated change, particularly when accompanied by improved protocol adherence. Segmented regression ITS analysis will then be used to provide formal statistical inference by estimating the pre-intervention baseline trend, the immediate post-intervention level change, and the change in monthly trend during the intervention period. The overall effectiveness of the QI project will be assessed by integrating primary outcomes, process measures, and balancing measures. The intervention will be considered to have achieved its intended goals if reductions in the antibiotic use rate and/or AUR are observed, accompanied by improved protocol adherence, without concurrent increases in the incidence of late-onset sepsis, in-hospital mortality, or the antibiotic re-initiation rate.

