**2) Preparation period (January 2026 to March 2026):**

This phase encompasses baseline data analysis, investigation of drivers of antibiotic use, development of the intervention package, staff training, and establishment of a multicenter data coordination mechanism.

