### Study setting and participants

2.3

This study is conducted concurrently across five NICUs in the Suqian region: Suqian First Hospital, Sihong Hospital, Sihong First Hospital, Shuyang Hospital of Traditional Chinese Medicine, and Siyang Hospital. These institutions serve as the primary referral centers for neonatal care within the region. The annual number of NICU discharges for each participating center in 2024 is presented in Table 1.

**Table 1 T1:** Characteristics of participating neonatal intensive care units in 2024.

Institution	Hospital level	Annual NICU admissions
Suqian First Hospital	Tertiary	862
Sihong Hospital	Tertiary	524
Sihong First Hospital	Secondary	395
Shuyang Hospital of Traditional Chinese Medicine	Tertiary	872
Siyang Hospital	Tertiary	484

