### Sample size considerations

2.4

As this study is a QI initiative with monthly aggregated data as the primary unit of analysis, no formal sample size or power calculation based on individual-level hypotheses was performed. The study design includes 12 consecutive monthly data points before and after the intervention. Methodological literature indicates that ITS analyses typically require a minimum of 8–10 data points in both the pre- and post-intervention phases to establish stable baseline trends and detect meaningful changes over time (21, 22). Accordingly, the planned study design is considered sufficient to support statistical process control analyses and ITS regression modeling.

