### Baseline assessment and root cause analysis

2.5

Before developing the intervention, we conducted a structured baseline assessment using 2025 data, informed by multidisciplinary discussions with NICU staff to identify drivers of high antibiotic use.

Through process mapping and multidisciplinary review, several key factors contributing to antibiotic overuse were identified, including:

Lack of standardized criteria for initiating antibiotic therapy;Risk-averse approach to early-onset sepsis (EOS) risk assessment;Absence of a systematic 48–72-h antibiotic reassessment process;Insufficient monitoring and feedback mechanisms related to antibiotic use.

These contributing factors were synthesized into a fishbone diagram (Figure 1) and served as the conceptual framework for the design of the antimicrobial stewardship QI intervention bundle.

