#### Primary outcomes

2.7.1

Antibiotic use rate: the proportion of neonates who received at least one course of systemic antibiotic therapy during the study period;AUR: defined as the number of antibiotic days per 1,000 patient-days.

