#### Time series analysis

2.9.2

Monthly aggregated data are used as the analytical unit. Statistical process control P charts are applied to assess temporal changes in antibiotic use rates and to identify special-cause variation based on standard run chart rules.

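### The plan reads any special-cause signal after roll-out as support for the intervention, but a flat P-chart cannot tell a continuing decline from an effect

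*Protocol article*

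**What the plan says.** Section 2.9 sets out a sequence of evidence. P-charts come first, and their reading is fixed in advance: "Special-cause variation observed after implementation will be interpreted as process-level evidence supporting intervention-associated change, particularly when accompanied by improved protocol adherence". Segmented regression follows and is given the role of formal inference; it estimates the baseline trend, the level change and the slope change.

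Section 2.9.2 names the chart and the outcome: "Statistical process control P charts are applied to assess temporal changes in antibiotic use rates". The charts are meant to "identify special-cause variation based on standard run chart rules"; the rules themselves are not listed. Section 2.7.1 defines the charted outcome as "the proportion of neonates who received at least one course of systemic antibiotic therapy during the study period".

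On the series, section 2.4 says "The study design includes 12 consecutive monthly data points before and after the intervention". Section 2.2 places a three-month preparation period (January to March 2026) between the two segments. Section 2.5 lists among the causes of overuse at baseline: "Absence of a systematic 48–72-h antibiotic reassessment process".

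**The concern.** The sentence in 2.9 is a rule of inference, not a description of a chart. As worded, a signal in either direction qualifies. A signal produced by a decline that started in 2025 also qualifies, and so does a signal that the ITS does not confirm.

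The plan itself allows for a baseline trend, since the regression has a term for it. The chart has none. With a flat centre line, months that continue an earlier downward drift fall below the line and form runs, which the plan would then cite as support.

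The qualifier about adherence gives little protection. Section 2.7.3 defines adherence as completing the initiation assessment and the 48–72-h reassessment as the intervention specifies. Section 2.5 records that no systematic reassessment and no standard initiation criteria existed at baseline. Adherence should therefore rise with roll-out whether or not prescribing changes.

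At stake is a report that cites a chart signal and better adherence as agreeing evidence when both would be expected under a continuing decline and no effect.

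**Working it through.** The plan states no false-signal rate, so there is no figure to reproduce. The check simulates the charted outcome with no intervention effect.

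**Inputs from the protocol**
- Monthly denominator, from Table 1 (section 2.3): 862 + 524 + 395 + 872 + 484 = 3,137 a year; 3,137 / 12 ≈ 261 a month, pooled.
- Months 0–11 are baseline, 12–14 the preparation gap, 15–26 intervention (sections 2.2 and 2.4).

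**Assumptions, because the protocol gives no figure**
- Baseline use rate p₀ of 60%, 70% or 80%.
- Prior linear decline d of 0, 0.2, 0.3 or 0.5 percentage points a month, continuing unchanged through roll-out.
- Independent binomial months.
- Signal: six or more consecutive intervention months below the median of the 12 baseline months.

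**Model.** Count in month t ~ Binomial(261, p₀ − d·t), 40,000 series per scenario. The lower three-sigma limit is p̄ − 3·√(p̄(1 − p̄)/261), with p̄ the baseline mean. The ITS is ordinary least squares with intercept, time, level change and slope change, tested two-sided at 5%.

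**Rough check by hand.** The midpoints of the two segments are 15 months apart (5.5 and 20.5). At p₀ = 70% the monthly SD is √(0.7 × 0.3 / 261) = 2.8 points. The displacement at mid-intervention is therefore 15 × 0.2 = 3.0 points (1.1 SD), 15 × 0.3 = 4.5 points (1.6 SD) or 15 × 0.5 = 7.5 points (2.6 SD). A month that far down falls below the line far more often than one time in two, so long runs follow.

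**Results with no intervention effect**

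| Prior decline, points/month | Downward run of 6, p₀ 60–80% | Point below lower 3-sigma, p₀ 70% | ITS level change | ITS slope change |
|---|---|---|---|---|
| 0 | about 10% | 3% | about 5% | about 5% |
| 0.2 | 64–73% | 35% | about 5% | about 5% |
| 0.3 | 87–93% | 69% | about 5% | about 5% |
| 0.5 | 99–100% | 99% | about 5% | about 5% |

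With the baseline mean as centre line the run-of-six figures are 65–75%, 89–94% and above 99%.

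**Sensitivity to the unstated rules**
- Stricter rules in either direction (run of 8, trend of 6, or a 3-sigma point; baseline mean; p₀ 50–80%): 71–85% at 0.25 points a month and 99.8–100% at 0.5.
- Centre line from all 24 months, p₀ 65%, downward run of 6: 41% at 0.25 and 85% at 0.5.

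**Effect of tying the signal to the ITS.** Requiring the downward run and a downward ITS level or slope change with a 95% CI excluding zero gives false support in about 1% of series with no trend and about 4–5% under the three declines.

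**The case against.** The strongest reply is that the hierarchy is already stated. Section 2.9 treats the chart as process-level support, describes its signals as only possibly linked to the intervention, and gives formal inference to a regression that models the trend. The success criterion in the same section does not name chart signals. This stands, and it limits the consequence. A reader might infer that a false chart signal could by itself produce a declared success; the text does not support that. What the hierarchy does not do is change the sentence, which still counts an unconfirmed signal as support.

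Other stronger readings also fail:
- **That the chart signals readily with no effect and no trend.** The downward run-of-six rate is about 10% and the lower 3-sigma rate about 3%. Looser rules counting both directions (run of 6 or trend of 5, with or without 3-sigma) give 25–29%. Stricter ones with a 24-month centre line give about 5%. The rules may be listed in a fuller document, so their absence is no fault here.
- **That almost any modest decline triggers a signal.** Near-certainty needs about 0.5 points a month, a fall of 7.5 points between segment midpoints. The protocol reports no decline in these units.
- **That binomial limits would be misapplied to the antibiotic utilization rate (AUR).** Section 2.9.2 applies P-charts to the antibiotic use rate, which section 2.7.1 defines separately as a proportion of neonates. The broader wording in 2.9 is too thin a basis for a claim about an AUR chart.

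**Conclusion.** The point holds as a defect in one interpretation sentence. Under a pre-existing decline of 0.2 to 0.5 points a month and no intervention effect, a flat P-chart of the use rate would give the supporting signal in roughly two-thirds to nearly all series, while each ITS term stays near its nominal 5%. The adherence qualifier does not separate these cases from a real effect.

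The sizes rest on an assumed baseline use rate, assumed slopes, a linear trend, independent months and a run-of-six rule. The direction of the result does not depend on the exact rule, as the sensitivity figures show. The consequence is over-reading of supporting evidence; the formal analysis is not affected.

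**What to change.** Replace the interpretation sentence in section 2.9 with a rule to this effect: the chart's centre line and limits are fixed from the 12 baseline months; a post-implementation signal counts as supporting evidence only if it is downward and the ITS level or slope change for the same outcome has a 95% CI excluding zero in the same direction; any other signal is reported as descriptive.

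Overdispersion-adjusted (Laney P′) limits are an optional refinement. At 70% use with no trend, an assumed extra between-month SD of 2–3 points raises the lower 3-sigma rate from 3% to 12–26%. Laney limits bring this to about 5–8% if the adjustment factor is not allowed below 1, and to 9–10% otherwise. They do not cure the trend problem.

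Projecting the baseline trend as the chart's centre line is tempting but should be avoided. At 70% use with no trend and no effect, it raises the false downward run-of-six rate from about 10% to 29% and the lower 3-sigma rate from 3% to about 20%, because a 12-month slope is extrapolated 4 to 15 months past its last point.

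The cost is one sentence and no new data. The downside is that fewer chart signals can be cited as support.

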**Methods:**

This ongoing study uses a multicenter, before-and-after interrupted time series (ITS) design across five NICUs in the Suqian region. A bundled ASP intervention is being implemented, comprising standardized early-onset sepsis risk stratification, mandatory 48–72-h antibiotic reassessment, protocolized empirical antibiotic regimens, and a two-tier governance structure supported by monthly Plan–Do–Study–Act cycles. Monthly aggregated data are collected during a 12-month baseline period (2025) and a 12-month intervention period (2026–2027). Primary outcomes are the antibiotic use rate and the antibiotic utilization rate (days of therapy per 1,000 patient-days). Balancing measures include the incidence of late-onset sepsis, in-hospital mortality, and antibiotic re-initiation rate. Process adherence is monitored as a key implementation indicator. Segmented regression ITS analysis and statistical process control charts are used to evaluate the intervention effect.

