#### Interrupted time series analysis

2.9.3

Segmented regression models are used to perform ITS analyses for primary outcome measures, estimating both immediate changes in level following intervention implementation (level change) and changes in trend over time before and after the intervention (slope change). Effect estimates are reported with 95% confidence intervals.

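### The efficacy part of the success rule needs only an observed fall in either primary outcome and is not tied to an interrupted time series contrast or its confidence interval

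*Protocol article*

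**What the plan says.** Section 2.9 sets out three steps. Control charts come first. After them, "Segmented regression ITS analysis will then be used to provide formal statistical inference", covering the baseline trend, the level change and the change in slope. The section then gives a separate decision rule. On efficacy, the intervention is judged to have met its goals "if reductions in the antibiotic use rate and/or AUR are observed". The rule also sets conditions on process and safety: adherence must improve, and none of three balancing measures (late-onset sepsis, mortality, restarting of antibiotics) may rise.

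Section 2.9.3 applies segmented regression to the primary outcomes, "estimating both immediate changes in level following intervention implementation (level change) and changes in trend over time", and adds: "Effect estimates are reported with 95% confidence intervals". The abstract and section 2.7.1 name two primary outcomes, the antibiotic use rate and the antibiotic utilization rate (AUR). Nothing in the article links the intervals of section 2.9.3 to the decision rule of section 2.9, says whether level or slope decides, or says how two primary outcomes share the error rate.

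**The concern.** The rule decides the study's headline conclusion, but as worded it does not use the inference planned for that purpose. Three features combine.

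- An observed reduction is a direction. With no effect, an estimate falls below zero half the time.
- Either outcome is enough, so there are two chances.
- The wording does not exclude a plain comparison of the two years. A decline already under way before the programme could then be credited to it, which is what the Discussion says the ITS design guards against.

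This is not a detail left to an analysis plan. The article itself states the criterion, and a later plan that required an interval would change that criterion, not fill it in.

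**Working it through.** The article states no error rate or power for this rule, so there is no figure to reproduce.

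**Inputs from the article.** Two primary outcomes (abstract, 2.7.1); two ITS coefficients per outcome (2.9.3); 12 monthly points before and 12 after (2.4); a three-month preparation gap (2.2). **Assumed:** the correlation ρ between the two outcome estimates; symmetric errors; independent monthly errors wherever an interval or standard error is used.

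**1. Direction only, no effect.** P(at least one of two falls) = 1 − [1/4 + arcsin(ρ)/(2π)].

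| ρ | P |
|---|---|
| 0 | 75.0% |
| 0.5 | 66.7% |
| 0.8 | 60.2% |
| 0.9 | 57.2% |
| 1 | 50.0% |

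Simulation of 40,000 null series per setting (12 months, 3-month gap, 12 months, no trend) agrees at ρ = 0, 0.5, 0.8 and 0.9. The difference in period means gives 74.9%, 66.6%, 60.4% and 57.3%; the sign of the ITS level change gives 75.0%, 66.5%, 60.2% and 57.3%. If a downward sign in either level or slope counted, the figure would be about 78–92%.

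**2. The whole rule.** Treat the adherence condition as met and the three balancing measures as independent of each other and of efficacy.

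- Read as no rise in the point estimate, each 50:50: 0.5³ = 0.125. Then 0.50 × 0.125 = 6.3% and 0.75 × 0.125 = 9.4%.
- Read as no significant rise, one-sided 2.5% each: 0.975³ = 0.927. Then 0.50 × 0.927 = 46% and 0.75 × 0.927 = 70%.

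**3. Crude before-after fall.** With months numbered from January 2025, the period midpoints are 6.5 and 21.5, which are 15 months apart. A pre-existing decline of 1% per month (assumed) gives 1 − 0.99¹⁵ = 14% with no intervention effect. In the simulation, a decline of 0.05 residual SD per month (assumed) met the efficacy part 98–99.9% of the time when judged by period means. The ITS level change was unaffected.

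**4. If the interval decided.** False success on efficacy, no effect:

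- Level-change 95% interval below zero in either outcome, unadjusted: 1 − 0.975² = 4.9% at ρ = 0; simulated about 4.5% at 0.5, 3.9% at 0.8 and 3.5% at 0.9.
- Level or slope interval below zero in either outcome: simulated about 7–9%; 1 − 0.975⁴ = 9.6% if all four were independent.
- Level-change interval below zero in both outcomes: at most 1.4% for ρ up to 0.9.

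**5. Precision of two candidate contrasts**, in residual SDs, by ordinary least squares. The sum of squares of 12 consecutive months about their mean is 143.

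- Level change at April 2026 (month 16): variance = [1/12 + 9.5²/143] + [1/12 + 5.5²/143] = 0.714 + 0.295 = 1.009; SE = 1.00.
- Mean difference from the counterfactual over April 2026 to March 2027 (level + 5.5 × slope change, April 2026 as month 0): variance = 1/12 + [1/12 + 15²/143] = 0.083 + 1.657 = 1.740; SE = 1.32.

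**The case against.** The rule is a conjunction, and 50–75% describes only one part of it. That stands. A reader might infer that an ineffective programme would be declared successful 60–75% of the time, and the article does not support that. On one reading of the balancing conditions the joint figure is about 6–9%. That low figure is no evidence of a sound efficacy test, however. The same reading would reject a harmless, effective programme 1 − 0.5³ = 87.5% of the time. The adherence condition also adds little, because it scores a reassessment process that section 2.5 reports as absent at baseline.

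Both outcomes measure antibiotic exposure in the same units and months, so a correlation above 0.8 is plausible. That stands too, and is why the range must run down to 50%.

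A reader might also infer that the article adopts a crude before-after comparison. It does not. Section 2.9 introduces the ITS analysis just before the rule, and an observed reduction may be meant as the ITS result. The text leaves this open, so the crude reading is permitted but not chosen, and the 14% needs an assumed trend as well. Even on the favourable reading, the rule names neither the contrast nor the interval.

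Multiplicity methods and exact contrasts are often left to an analysis plan. That limits the point to what the article itself fixes: a direction, in either of two outcomes, without the interval.

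**Conclusion.** The point holds for the efficacy part of the success rule. As written, that part is met by chance 50–75% of the time with no true effect. This rests on a direction-only reading, symmetric errors and an assumed correlation between 0 and 1. The chance of declaring overall success cannot be fixed from the text: it is about 6–9% or about 46–70%, depending on how the balancing conditions are read and assuming that they are independent. On neither reading do those conditions show that antibiotic use fell. The interval-based rates assume no autocorrelation.

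This should be fixed, but it does not invalidate the study. It is a quality improvement initiative, and effect estimates with 95% intervals are reported whatever label the rule yields, so readers can judge the effect for themselves.

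**What to change.** Amend the rule in section 2.9 so that a reduction means that the 95% confidence interval of one pre-named ITS contrast lies entirely below zero. Then choose one of the following:

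- require it in both primary outcomes; or
- allow either one, with Holm adjustment across the two.

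The contrast may be the level change, or the model-based mean difference from the counterfactual over April 2026 to March 2027 (level + 5.5 × slope change, April 2026 as month 0). Report the remaining coefficients descriptively. Settle this before intervention-period outcomes are analysed.

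The change is one of wording; both contrasts come from coefficients already planned. The price is a stricter criterion, and the choice of contrast is a trade-off. The mean difference summarises the whole intervention year but extrapolates the 12-month baseline further, with an SE of about 1.32 residual SDs against 1.00 for the level change. With 20 residual degrees of freedom, 80% power needs an effect of roughly (2.086 + 0.860) × SE: about 3.9 residual SDs for the mean difference and 3.0 for the level change, for a single outcome and before any Holm adjustment. Requiring both outcomes lowers power further. Section 2.4 gives no power calculation, so this cost should be weighed when the contrast is chosen.
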